Research evaluating TF-CBT in older children and adults has established an empirical base supporting the efficacy of the intervention [16]. Given the rapid development seen in younger children it is necessary to evaluate this paradigm separately to adults and older children. To date, there has only been one small pilot clinical trial examining TF-CBT in younger children, where children were allocated either to receive 12 sessions of manualised TF-CBT or to a waitlist control group [17]. The results of this study, conducted in New Orleans, USA, supported the feasibility and impact of developmentally-tailored CBT with a large effect size and treatment gains maintained at the 6-month follow-up. However, the results from this study are unlikely to be generalisable, particularly within the UK, given that the trial was conducted in an underprivileged, low social-economic group in an urban American setting [17]. Based on our previous work with older children and adolescents, aged 8 to 17 years, showing that TF-CBT improves symptoms of PTSD, anxiety, and depression, as compared to a waitlist control group, we adapted this programme [18] to provide a 12-session intervention suitable for young children (TF-CBT-YC) aged 3 to 8 years, following a single-incident traumatic event.

This study has been designed to answer three main questions. First, do children, diagnosed with PTSD, experience symptom reduction to sub-clinical levels following TF-CBT-YC? Secondly, is the treatment feasible and acceptable? Thirdly, is the cost of implementing TF-CBT-YC likely to represent a saving to the UK National Health Service (NHS) in terms of reducing the overall costs associated with service use post-trauma?

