## Methods/Design

### Study design

This study is a two-arm pilot randomised controlled trial (RCT) comparing TF-CBT-YC with treatment as usual (TAU). A half-crossover design will be employed such that participants allocated to the TAU arm will be offered the intervention after a 12-week waiting period if still indicated. Participants will be assessed 4 times during the study - at baseline, at post-TAU or -treatment, and at 3-month and 12-month follow-up for participants allocated to the treatment condition (see Figure 1). The post-treatment assessment will be conducted in the week following treatment completion and the post-TAU assessments will be at a comparable duration in the TAU arm.

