### Participant allocation

Eligible participants will be randomised to TF-CBT-YC or TAU using a minimisation procedure suitable for small samples, constrained by age group (3 to 5 years or 6 to 8 years), gender, and initial clinical severity as assessed on the DIPA (high and low). These variables were selected because of their likely influence on treatment response. Randomisation will occur after consent has been taken and baseline measures have been completed. The trial team will Email the independent statistician (PW) details of the three stratifiers and, using the minimisation programme MinimPy [22], the statistician will randomise the participant and Email the results to the trial coordinator. Following randomisation, participants will be notified of their allocation by telephone, which is subsequently confirmed in writing. See Figure 2 for the Consolidated Standards of Reporting Trials (CONSORT) diagram.

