### Health economics measures

Data collection for the health economic evaluation will take a broad societal perspective, recording all hospital, community health and social services usage. Productivity losses resulting from time off work by parents or carers as a consequence of their child’s PTSD will be calculated using the human capital approach, a multiplication of days off work due to illness by the individual’s salary level [31]. Data will be collected using a structured questionnaire adapted for this study but based on the Child and Adolescent Service Use Schedule (CASUS), an instrument previously used in a trial of CBT for major depressive disorder in adolescents [32]. Data on TF-CBT-YC contact time and on indirect time (for example, supervision) spent delivering the intervention will also be collected. Cost information will be taken from national publications. Together, these data will allow us to test our resource utilisation instruments and permit preliminary estimates of TF-CBT-YC’s potential cost-effectiveness.

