### Methodological aspects

#### Data collection

Quantitative outcome variable data for the trial will be collected at baseline, post-treatment, 3-month and 12-month follow-up. Qualitative interview data on treatment completers will be collected at 3-month follow-up, except in the case of participants who drop out earlier who will be followed-up as appropriate. Health economics data will be collected retrospectively (for the preceding 3-months) at all 4 assessment time points.

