### Statistical analysis plan

Initial analyses of the quantitative primary and secondary outcome data will be conducted on an intent-to-treat basis, with subsequent analyses being per protocol (based on attendance at 50% of offered sessions), and carried out by the trial statistician (PW) following CONSORT standards [33]. Comparisons will be made across groups on all outcome measures. For the continuous scales, repeated measures analyses of variance (ANOVAs) will be used without adjustment in the first instance, and then adjusting for baseline levels of the relevant measures as covariates if indicated. For the caseness measure of PTSD, non-parametric analyses will be used (for example, Chi square/Fisher’s exact test).

Qualitative interview data will be analysed using thematic analysis [34], facilitated by NVivo 8 software (QSR International). For the health economic data, mean estimated treatment costs in the two trial arms will be compared using ANOVA and the robustness of the parametric tests confirmed using bootstrapping. The primary analysis will explore cost-effectiveness in terms of loss of PTSD diagnosis (that is 'recovery'). If a significant difference in the primary outcome is observed between the two treatment arms, cost-effectiveness will be explored through calculation of an incremental cost-effectiveness ratio and sensitivity analyses.

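### The planned cost comparison leaves out each child's baseline 3-month cost, which is already collected; adjusting for it could add precision at almost no cost

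*Protocol article*

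**What the plan says.** Under Statistical analysis plan, the protocol article says that "mean estimated treatment costs in the two trial arms will be compared using ANOVA", with "the robustness of the parametric tests confirmed using bootstrapping". It names no covariate for costs. The same section does provide for "adjusting for baseline levels of the relevant measures as covariates if indicated", but that clause belongs to the sentence on the continuous scales; costs have their own sentence without it.

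Under Data collection: "Health economics data will be collected retrospectively (for the preceding 3-months) at all 4 assessment time points". Study design confirms that baseline is one of the four: "Participants will be assessed 4 times during the study - at baseline, at post-TAU or -treatment". Health economics measures gives the scope of the data as "recording all hospital, community health and social services usage", plus parental productivity losses and the time spent delivering TF-CBT-YC.

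Participant allocation minimises on age band, gender and DIPA severity. Prior service use is not a factor. Background lists as the third main study question whether the treatment is likely to save the NHS money by "reducing the overall costs associated with service use post-trauma".

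**The concern.** The plan collects a cost for each child before randomisation, with the same questionnaire and recall length as the post-treatment cost, and then gives it no part in the arm comparison. Prior service use may vary widely in this population. Children come through emergency departments or community referral, with acute or chronic PTSD, and TAU children may keep any therapy they already have. That last feature also suggests that some baseline use will carry over into follow-up.

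With so few children, a handful of heavy users falling in one arm by chance would move the unadjusted cost difference, and with it the numerator of any incremental cost-effectiveness ratio. Bootstrapping the unadjusted difference deals with skewed costs. It neither removes a baseline imbalance nor recovers precision.

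**Working it through.** **Inputs from the protocol.** 44 children, 22 per arm; 17 per arm evaluable after 20% attrition (Participants; Determination of sample size). The protocol gives no power, effect size or variance for costs, and no correlation (rho) between a child's baseline and follow-up cost. Rho is therefore an assumption, shown from 0 to 0.7.

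**The plan's own figure.** The stated sample size concerns recovery, not cost. With recovery of 45% versus 89%, 17 per arm and a one-sided 5% Fisher test, exact power is 81.4%, which agrees with the stated 80%. Attrition: 17 / 0.8 = 21.25, rounded up to 22. Both figures reproduce, so 17 and 22 per arm are used below.

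**Chance imbalance in baseline cost.** In SD units, the difference in arm means has standard deviation sqrt(2/n), with n per arm, if prior cost is unrelated to the minimisation factors.

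| n per arm | SD of imbalance | P(imbalance > 0.3 SD) | P(imbalance > 0.5 SD) |
|---|---|---|---|
| 17 | 0.34 | 38% | 15% |
| 22 | 0.30 | 32% | 10% |

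Under ANOVA, an imbalance of d SD shifts the expected cost difference by rho × d. For d = 0.3 the shift is 0.09, 0.15 or 0.21 SD at rho 0.3, 0.5 or 0.7.

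**Precision.** The variance of the adjusted difference relative to ANOVA is (1 − rho²) × [1 + 1/(2n − 4)]. The second factor is the price of estimating the slope: 1 + 1/30 = 1.033 at n = 17 and 1 + 1/40 = 1.025 at n = 22.

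| rho | n = 17 | n = 22 | Change in standard error |
|---|---|---|---|
| 0 | 1.03 | 1.03 | 1 to 2% wider |
| 0.3 | 0.91 × 1.033 = 0.94 | 0.93 | about 3% narrower |
| 0.5 | 0.75 × 1.033 = 0.78 | 0.77 | about 12% narrower |
| 0.7 | 0.51 × 1.033 = 0.53 | 0.52 | 27 to 28% narrower |

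Break-even is where (1 − rho²) × [1 + 1/(2n − 4)] = 1. This gives rho² = 1/31, or rho = 0.18, at n = 17, and rho² = 1/41, or rho = 0.16, at n = 22: about 0.17. At rho 0.5, 17 adjusted children per arm carry the information of 17 / 0.775 = 21.9 unadjusted.

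**Skewed costs.** A simulation of 10,000 trials at 17 per arm used lognormal costs with log-scale correlations of 0.3, 0.5 and 0.7. The variance ratios were 0.94, 0.78 and 0.53. The correlation of the baseline imbalance with the ANOVA result was 0.24, 0.42 and 0.64, and about zero after adjustment. With the correlation set on the raw cost scale instead, the ratio was about 0.90 at 0.3 and 0.70 at 0.5. Both estimators centred on the true difference, so the gain does not depend on normally distributed costs.

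**The case against.** The strongest reply is that nothing here is wrong. A comparison of randomised means is unbiased, and its standard error already allows for chance imbalance. Lost precision and exposure to imbalance are largely one effect seen from two sides. That stands. A reader might infer that the planned result is biased, or that imbalance could reverse its sign. The documents do not support either: randomisation rules out the first on average, and no expected cost difference is given against which to show the second.

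Nor can this be called a power shortfall, since the protocol sets no power target for costs.

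The gain also rests on an unknown correlation that may be low. On the emergency-department route, children with PTSD are invited at 3 months post-trauma (Recruitment), so their baseline look-back covers much of the acute injury care. The post-treatment window covers later service use and, in one arm, the therapy itself. This stands too, and is why the range starts at zero.

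Two objections carry less weight. A condensed article may leave covariates to a fuller plan, but this one names the cost method and provides for baseline adjustment only for the symptom scales; the sensitivity analyses it mentions are tied to the conditional cost-effectiveness ratio. The reference to treatment costs could mean therapy delivery alone, in which case prior service use would matter less. The scope of data collection and the third study question point to total service cost.

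**Conclusion.** The point holds as a missed improvement in efficiency, not as an error of validity. ANOVA with a bootstrap check is a sound comparison that leaves unused a baseline value the trial already plans to collect. At 17 per arm the possible change in variance runs from about 3% worse at zero correlation, through 6% better at 0.3 and 22% better at 0.5, to 47% better at 0.7. Which of these applies cannot be settled from the documents.

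The conclusion assumes that the comparison concerns total costs and that baseline resource use is recorded as planned. It merits consideration rather than insistence, because Health economics measures describes the economic output as preliminary estimates and a test of the resource-use instruments.

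**What to change.** Under Statistical analysis plan, replace the cost sentence with wording such as: *Total costs (service use plus TF-CBT-YC delivery) over the 3 months to the post-treatment assessment will be compared between arms by regression on trial arm, adjusting for the child's cost in the 3 months before baseline, with bootstrap confidence intervals for the adjusted mean difference. The adjusted difference will be used in any incremental cost-effectiveness ratio. The unadjusted comparison will be reported as a sensitivity analysis.*

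Delivery cost enters the follow-up cost only. The wording also settles which costs are meant, and fixing the model in advance removes any later choice between adjusted and unadjusted results.

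The change needs no new data, visits or children. It costs one degree of freedom and, if the correlation is zero, about 3% more variance.

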## Discussion

PTSD is a distressing and debilitating mental health condition. If left undiagnosed and untreated, PTSD can take a chronic course and lead to significant functional impairment [13]. TF-CBT is an evidence-based treatment with demonstrated efficacy for older children, adolescents and adults [25]. However, there is no evidence base for its efficacy in younger children. There has been a growing recognition of the need to develop an age appropriate treatment model for younger children; this exploratory RCT meets this objective. The timely nature of this trial is underscored by the inclusion of a preschool age criteria included in the recent DSM-5, reflecting the growing recognition that PTSD in this age group needs to be addressed.

Data evaluating the effectiveness of TF-CBT-YC will provide an initial step towards providing an empirical base for the treatment of young children with PTSD. If superiority to TAU can be demonstrated, the results from this trial will support the need for a fully powered definitive trial to examine TF-CBT-YC as the treatment of choice for young children with PTSD. Not only is this trial needed to examine efficacy, feasibility and acceptability, but the economic evaluation of this treatment will determine its cost-effectiveness over the medium to long term and, therefore, TF-CBT-YC’s applicability to delivery through NHS channels. Accordingly, TF-CBT-YC has the potential to bring benefits to young children affected by PTSD, but also to the health system more broadly.

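### The cost-effectiveness ratio is calculated only if the primary outcome is significant, which conflicts with the protocol's unconditional promise of a preliminary estimate and selects the effect on which the ratio rests

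*Protocol article*

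**What the plan says.** The economic paragraph of the Statistical analysis plan contains three statements:

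- Costs, without a condition: "mean estimated treatment costs in the two trial arms will be compared using ANOVA and the robustness of the parametric tests confirmed using bootstrapping".
- Cost-effectiveness, without a condition: "The primary analysis will explore cost-effectiveness in terms of loss of PTSD diagnosis".
- The ratio, with a condition: "If a significant difference in the primary outcome is observed between the two treatment arms, cost-effectiveness will be explored", by "calculation of an incremental cost-effectiveness ratio and sensitivity analyses".

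Other sections set the expectation. The Background lists as the third main question: "is the cost of implementing TF-CBT-YC likely to represent a saving to the UK National Health Service (NHS"). Health economics measures says that the data will "permit preliminary estimates of TF-CBT-YC’s potential cost-effectiveness". The Discussion goes further: "the economic evaluation of this treatment will determine its cost-effectiveness over the medium to long term". None of these depends on the primary result. Determination of sample size says that the main aim is to resolve protocol and procedural uncertainties before a larger evaluation.

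**The concern.** Cost-effectiveness is a matter of estimation. It depends on incremental cost and incremental effect taken together, with their uncertainty, and not on whether the effect alone passes a 5% test. A treatment can be good value with an uncertain effect, or poor value with a significant one.

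The condition has two consequences. After a non-significant result, the ratio and its sensitivity analyses are not produced, although the protocol promises a preliminary estimate. After a significant result, the ratio's denominator is a recovery difference that has been selected for being large. For a given positive cost difference, a larger denominator makes the treatment look better value than it is. Planning for the definitive trial would then rest on an absent or a selected estimate.

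**Working it through.** **Inputs.** From Determination of sample size: recovery 45% (TAU) v 89% (TF-CBT-YC), 17 evaluable per arm, 22 recruited per arm, 80% power, 1-tailed 5%. From Statistical analysis plan: chi-square or Fisher's exact test, given as examples and without stating one- or two-sided. I therefore show the one-sided chi-square, the one-sided Fisher and the two-sided Fisher. The two-sided chi-square agrees with the one-sided Fisher to within 0.1 percentage point on the probability of no ICER in every row below.

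**Step 1: the plan's own figure.** At 17 per arm and 45% v 89%, exact power of the one-sided Fisher test is 81.4%, which agrees with the stated 80%. For attrition, 17 / (1 − 0.20) = 21.25, rounded up to 22. The sample size is not in question.

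**Step 2: how often there is no ICER, and how far the difference is inflated.** Let A ~ Bin(n, p_TAU) and B ~ Bin(n, p_CBT) be the numbers recovered, and D = (B − A)/n. Summing over all pairs (A, B):

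- P(no ICER) = 1 − P(p-value ≤ 0.05)
- inflation = E[D | p-value ≤ 0.05] / (p_CBT − p_TAU)

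Each cell gives P(no ICER), then inflation:

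| True rates | n per arm | chi-square, 1-sided | Fisher, 1-sided | Fisher, 2-sided |
|---|---|---|---|---|
| 45% v 89% (plan) | 17 | 10.3%, 1.07 | 18.6%, 1.11 | 29.7%, 1.16 |
| 45% v 89% (plan) | 22 | 4.3%, 1.03 | 9.4%, 1.05 | 15.5%, 1.08 |
| 45% v 75% (assumed) | 17 | 40.6%, 1.35 | 54.9%, 1.47 | 68.7%, 1.60 |
| 45% v 75% (assumed) | 22 | 34.0%, 1.26 | 47.2%, 1.35 | 59.4%, 1.45 |
| 45% v 70% (assumed) | 17 | 53.0%, 1.56 | 66.8%, 1.72 | 78.7%, 1.89 |
| 45% v 70% (assumed) | 22 | 48.6%, 1.45 | 61.5%, 1.57 | 72.6%, 1.70 |

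Example, plan rates, 17 per arm, one-sided Fisher: E[D | significant] = 0.488, and 0.488 / 0.44 = 1.11.

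**Step 3: what this does to the ratio.** The ICER is ΔC/D, so for a fixed positive cost difference ΔC its relative change is (p_CBT − p_TAU) × E[1/D | significant] − 1. At the plan's rates this runs from 4% too high (one-sided chi-square, 22 per arm) to 11% too low (two-sided Fisher, 17 per arm). The slight rise occurs because the average of 1/D exceeds 1 over the average of D, and this offsets the small inflation. At the assumed 30- and 25-point differences the ratio is too low in every cell, by 16% (one-sided chi-square, 22 per arm, 30 points) to 46% (two-sided Fisher, 17 per arm, 25 points).

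**Step 4: one concrete case.** With 8 of 17 recovered on TAU, the one-sided Fisher test needs 14 of 17 on TF-CBT-YC (p = 0.035; 13 of 17 gives p = 0.079). An observed benefit of 5/17, or 29 points, would yield no ICER.

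**The case against.** Four arguments favour leaving the plan as it is.

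1. *Only the ratio and its sensitivity analyses are conditional.* This stands. Mean costs are compared whatever the result, and the recovery difference is the primary outcome and will be reported anyway. A reader might infer that the third study question often goes unanswered. The document does not support that: the question is about a saving to the NHS, and the unconditional cost comparison bears on it directly.
2. *At the plan's own effect the harm is modest.* This also stands. A reader might take the 67% to 79% and the 1.7 to 1.9 as the expected loss. Those figures need a true 25-point difference, 17 per arm, and a test other than the one-sided chi-square. The 25- and 30-point differences are assumptions. They are worth showing because the design rates come from a trial in older children against a waiting list, whereas TAU children here may continue or start other therapy (Interventions).
3. *A ratio with a denominator near zero is unstable, so a condition protects against a meaningless number.* The instability is real. It argues for showing cost and effect jointly, not for reporting nothing, and a significance test is a poor guard because it also removes clearly positive differences (Step 4).
4. *The economic work is preliminary, and detail belongs in a separate health-economics plan.* Acceptability curves and baseline-cost adjustment may well be left to such a plan, and their absence is no fault. The condition is different, because the article states it as a rule.

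**Conclusion.** The point holds in a limited form. The condition on the ICER contradicts the sentence just before it, the Health economics measures section and the Discussion, and it sits badly with a pilot not meant as a test of efficacy. Under the design assumptions the loss is 4% to 30% of trials without an ICER. The inflation of the recovery difference is 1.03 to 1.16 times, with little net bias in the ratio itself. The effect becomes serious only if the true difference is well below 44 points: at an assumed 25 to 30 points, 34% to 79% of trials give no ICER and the difference is inflated about 1.3 to 1.9 times. These figures assume independent binomial outcomes, equal arms, a TAU recovery of 45%, and a cost difference that does not vary with the observed effect. The change is worth making because the rule has no analytic justification and is cheap to remove.

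**What to change.** Delete the significance condition. State that, for the randomised period and whatever the primary p-value, the report will give incremental cost, incremental recovery, and their joint uncertainty from a bootstrap that resamples each child's cost and outcome together, with the ICER where it can be interpreted. Label the result preliminary. Limiting it to the randomised period keeps the comparison between arms, since TAU children may be offered TF-CBT-YC afterwards.

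The cost is small but not nil. No new data are needed, but bootstrapping is at present planned only as a check on the cost tests, so the joint version is a modest extra analysis. The intervals will be wide with 17 to 22 per arm, and the report should say so.
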